### Outcome Measures and Data Collection

#### Primary Outcome Measures

##### Fall Risk

*Fall risk* will be assessed using the CDC’s Stopping Elderly Accidents, Deaths, and Injuries fall risk checklist. It consists of 12 statements related to physical and psychological fall risk factors, with responses of either yes or no. If a person scores ≥4 points, it suggests that there is a risk of falling [2]. The sensitivity of this checklist for discriminating fallers and predicting future fallers among community-dwelling older adults is 73% to 80% [64].

##### Dynamic Balance

*Dynamic balance* will be assessed using the “Timed Up and Go” (TUG) and “Sit to Stand” (STS) tests suggested by the CDC [2] and the American Geriatric Society [65]. It is important to conduct >1 balance test, as some participants may be identified as at risk on one and not another [64]. The TUG test is a commonly used method for evaluating functional mobility and predicting the risk of falling [66,67]. The TUG test has been validated among older adults in the community [68]. The TUG test has been proven to be effective in assessing older adults at risk of falling, with a sensitivity and specificity of 87% [69]. The STS is reliable for various populations [70,71]. For the TUG test, participants will stand up from a standard armchair, walk at a normal pace for 3 m, return, and sit down again [72]. Participants who complete the TUG test in <12 seconds will be classified as having a low fall risk [73]. Then they will complete the STS. To begin, the participant should sit in the center of the chair, crossing their hands at the wrists and placing them on the opposite shoulder. They should keep their feet flat on the floor, their back straight, and their arms against their chest. Then, they should repeat the motion of standing up and sitting back down for 30 seconds. The results will be scored based on their age and sex as suggested by the CDC [2].

##### PA Measures

*PA* participants will have their activity levels monitored using ActiGraph GT9X Link wireless activity monitors for 7 consecutive days. These devices, which are triaxial accelerometers, will be worn on the nondominant wrist by all participants. The GT9X Link has a sample rate of 30-100 Hz and a dynamic range of ±8G. It also has a rechargeable battery that lasts up to 14 days and can store up to 4 GB of data for 180 days. Information is collected every minute. A sensor checks if the device is being worn or not. The GT9X Link gives accurate 24-hour measurements of PA, such as steps taken, energy expended, intensity, and the user’s position. Measuring PA through accelerometry is a reliable method (ICC=0.98), especially when assessing free-living individuals [74]. It has been validated through comparison with measurements of direct observation, energy expenditure, and sedentary behavior [75,76].

#### Secondary Outcome Measures

##### FRA Shifting

*FRA shifting* consists of (1) maladaptive shifting, which is moving from the rational quadrant into any other quadrant, and (2) adaptive shifting, which is moving from irrational, incongruent, or congruent into the rational quadrant [77]. We use the FRA matrix, a graphical grid categorizing levels of FOF (mind) and levels of balance (body) into four quadrants [22,23]: (1) *rational:* low FOF (short Falls Efficacy Scale-International [FES-I] ≤10) and normal balance (BBS ≤30), (2) *incongruent:* low FOF (short FES-I≤10) despite poor balance (BBS>30), (3) *irrational:* high FOF (short FES-I>10) despite normal balance (BBS≤30), and (4) *congruent:* high FOF (short FES-I>10) and poor balance (BBS>30).

##### Levels of FOF

*Levels of FOF* will be assessed using the short FES-I. It is a 7-item self-report questionnaire (English and Spanish version) that provides information on the level of concern about falls for a range of activities of daily living [78]. On a 4-point Likert scale, low-income older adults will be asked to rate their concerns about the possibility of falling when performing 7 activities such as dressing. The scores range from 7 to 28 [79]. Higher total FES-I scores indicate higher FOF [78]. Scores of 7 to 10 indicate low concern about falling, whereas scores of 11 to 28 indicate high concern about falling [80,81]. The short FES-I has been validated in community-dwelling older adults [80]. Cronbach α=.97 and ICC=0.979 among older adults [82].

##### Levels of Balance

Levels of balance will be assessed using the BBS. During the BBS, a piece of sturdy furniture or a standard walker will be placed within the participant’s reach to reduce the risk that FOF will contaminate performance and enable even frail people to participate. Individuals will stand as still as possible on the BTrackS Balance force plate with their hands on the hips and eyes closed [83]. After the test, there are three results: (1) baseline, postbaseline, and percentage of changes; (2) comparison with sex and age group; and (3) levels of fall risk. In comparison with the age group, the software uses the BBS Normative Database to compare the individual with others in their age group. The BBS score is dependent on age and sex but not body size so that the percentile rankings can be determined across various age groups and for men and women separately [84]. A scale from 0 to 100 represents the percentile ranking of the BBS. A score of 0 to 30 indicates a low fall risk (normal balance) [84].

##### Negative Self-Perceptions

*Negative self-perceptions* will be measured using the Brief Aging Perceptions Questionnaire, which consists of 17 items [84]. In the proposed study, we will calculate an overall negative perception score (range 17-85, as in the study by Fawsitt et al [85] and Freeman et al [86]) by summing all negative scales after reverse scoring positive subscales. In our pilot study (N=48), this measure’s Cronbach α was .64.

### Additional Measures of Interest

#### Social Determinants of Health

*Social determinants of health* from the PhenX tool kit include protocols related to demographics or participants’ characteristics including age, sex, education, history of falls, the number of comorbidities, access to health services, health literacy, and access to health technology [87].

#### Depression

*Depression* will be measured using the Patient Health Questionnaire-9. The Patient Health Questionnaire-9 (English and Spanish) is a valid and reliable tool for screening depression in older adults [88,89]. It has high internal consistency (Cronbach α=.89) [88,89]. Participants will score how often each symptom (eg, feeling tired) was present within the last 2 weeks. The total scores range from 0 to 27, with scores ≥10 indicating moderate depression [88].

#### Anxiety

*Anxiety* will be measured using the Geriatric Anxiety Inventory-Short form, which consists of 5 items, investigates 3 dimensions of anxiety (somatic, cognitive, and affective), and is rated on a 4-point Likert scale, ranging from 0 (not at all) to 3 (all the time) [90-92]. It has adequate internal consistency and validity for screening anxiety in older adults [93].

#### Incidence of Falls

We will measure the number of falls and near falls. A *fall* is defined as an unexpected event in which an individual comes to rest on the ground, floor, or a lower level. An *injurious fall* is defined as hospitalization for or receipt of outpatient care because of a fall [94,95]. A *near fall* is a stumble event or loss of balance that would result in a fall if sufficient recovery mechanisms were not activated. At least 2 compensatory mechanisms (eg, unplanned movement of the arms, legs, and trunk tilt) should be activated [96]. The number of falls and near falls will be assessed using a monthly fall log by low-income older adults and follow-up phone calls by RAs.

#### Exercise Adherence

A weekly exercise log is designed from our pilot work to record activity including the types and duration of exercise that low-income older adults performs at home. A weekly exercise log will be handed to the PC at the group exercise in the week after.

### Data Collection

Demographic data (eg, age, sex, living status, and education level), perceived general health, self-report of vision, medication use, urinary incontinence, and the number of falls in the past 6 months will be assessed at baseline to provide context about low-income older adults. A trained RA will perform all baseline and follow-up assessments and will be blinded to the group assignment. Low-income older adults will be instructed not to inform assessors of their group status. All questionnaires and tests (except the PA test) take approximately 60 to 90 minutes to complete, and no risks or discomfort were associated with the balance and PA tests in our pilot studies.

### Data Management and Integrity

Data files will be built on a password-protected computer using REDCap (Research Electronic Data Capture; Vanderbilt University), which will be housed on a secure university server [97,98]. RX (coinvestigator) and RAs will be responsible for data cleaning and will teach the data entry system to the study team members who will be recording data in REDCap. Following an initial audit, the data will be double entered, and files will be matched to verify the accuracy of the data for the first 5 participants, after which a random 5% (17/340) of the total sample will be double checked periodically throughout the study. The data will be systematically examined for out-of-range values and inconsistencies. We anticipate no more than 5% missing values on any 1 item, as data will be collected in person on site and via phone calls. Missing data will be identified and obtained during follow-up interviews or with follow-up contact with participants. We will create an audit trail to identify and correct issues, protect participants’ privacy, ensure confidentiality, and maintain data integrity [99]. If causes of error other than random variation are identified, we will modify or adjust our procedures and train team members as needed.

### Data Analysis

We will collect demographic information from the participants for the study. We will compare baseline variables, such as essential participant characteristics, primary, and secondary end points, to summarize the differences between the 2 groups at the start of the study (T1). For the analysis of categorical data and continuous data, the chi-square test and 2-tailed *t* test will be used. We use R (version 4.1.2; R Foundation) for data analyses, with a significance level of *P*=.05.

Aim 1 is to examine the effects of the technology-based PEER intervention on fall risk, dynamic balance, and accelerometer-based PA.

The hypotheses are as follows:

*H 1.1*: The PEER group will reduce the fall risk compared with the control group.*H 1.2*: The PEER group will improve the dynamic balance compared with the control group.*H 1.3*: The PEER group will improve accelerometer-based PA compared with the control group.

Data will be analyzed according to the intention-to-treat principle [100]. We will model the fall risk, dynamic balance, and accelerometer-based PA as longitudinal outcomes consisting of 4 measurements (baseline or T1, after program completion or T2, follow-up at 3 months or T3, and follow-up at 6 months or T4) using the longitudinal linear mixed model (LMM) [101]. The LMM allows all low-income older adults and their available data to be included in the analysis, even for unequal group sample sizes, and the group heterogeneity can be addressed in the variance structure of random effects. It is hypothesized that the PEER group will show improvement in all outcome measures over time. To test hypothesis *1.1*, between-arm differences for fall risk scores, the likelihood ratio test (LRT) [101] associated with LMM will be used from all follow-up assessment visits. Similarly, the LRTs will be used to test hypotheses *1.2* and *1.3* for between-arm differences for dynamic balance and PA, respectively. The CDC-recommended scoring scheme will be adopted to process fall risk, TUG, and STS data [102]. For example, the average score of the number of STS repetitions a person can complete is based on different age and sex groups [102].

Raw acceleration data from ActiGraph will be downloaded and converted to “.csv” files using ActiLife 6 Software (version 6.13.4; ActiGraph LLC). PA data will be processed using the R package *GGIR* (version 2.4-0). *GGIR* R package used to process multiday raw accelerometer data for PA research [103] includes (1) auto-calibration of acceleration signals according to local gravity [104], (2) detection of nonwear time, and (3) calculation of the average magnitude of dynamic acceleration corrected for gravity (ie, Euclidean Norm Minus One) over 5-second epochs and expressed in milli-gravitational units (mg) [105]. Nonwear time and sustained abnormally high accelerations will be imputed using the default settings [105]. The Euclidean Norm Minus One cut-off points will be used to estimate the total time spent in sedentary behavior, light intensity PA, and MVPA in participants.

For missing data treatment, the missing values will be imputed using the method of multiple imputations [106]. The maximum number of missing values within a scale will be based on the guidelines provided by the scale developers or based on a limit of 25% missing values. In the first analysis, all low-income older adults will be included according to their original group assignment [100]. Participants in the PEER group who completed at least 5 of the 8 group-based sessions will be included in the per-protocol analysis. Although every attempt will be made to ensure that low-income older adults complete all assessments, there may be some participant attrition over time. The missing data mechanism is assumed to be missing at random. The dropout patterns or missing data rates for the 2 arms will be examined to assess the differences. When possible, the models should be modified to account for relevant factors such as age, sex, general health perception, and the number of falls in the 6 months leading up to the baseline. To determine the impact of the PEER intervention during follow-up evaluations, the group-by-time interaction term will be incorporated into the model. Effect sizes (Cohen *d*) [107,108] will be calculated based on the estimated means and the pooled SD.

Aim 2 is to examine the effects of the intervention on FRA shifting and negative self-perceptions of aging.

The hypotheses are as follows:

*H 2.1*: The PEER group will have a more adaptive shifting compared with the control group.*H 2.2*: The PEER group will have a more positive shift in their perceptions of aging compared with the control group.

To test hypothesis *2.1* (FRA shifting), the 4 FRA quadrants will be determined by grid coordinates based on 2 continuous level measures (BBS and short FES-I scores). We will classify shifting into 2 types: maladaptive and adaptive shifting. Adaptive shifting is moving from irrational, incongruent, or congruent to rational. The outcome is a percentage of low-income older adults with baseline (T1) in irrational, incongruent, or congruent quadrants who end up in the rational quadrant after program completion (T2). Maladaptive shifting is a movement from rational to any other quadrant, and the percentage of low-income older adults will be calculated. After program completion (T2), the baseline FRA categories (T1) may remain the same or shift to a different FRA category. We will form a 4×4 contingency table for the 4 FRA categories at each follow-up time point (T3 and T4) to summarize the shifts. The standard 4×4 table analysis will be performed to examine the FRA shifting, either using a chi-square test or exact test, depending on the actual counts observed in the 4×4 table. The BBS and short FES-I scores will be collected in 4 planned visit time points (T1, T2, T3, and T3). We will use the Generalized Linear Mixed Model (GLMM) to analyze these 2 end points for assessing the difference between the PEER intervention and control arms on the shift of FRA categories [109]. Our longitudinal data on the PEER effects of different types of shifting on low-income older adults will contain repeated binary measures of the shifting status over time. The binomial GLMM with the logic link will allow us to assess the difference between the 2 arms in FRA shifting, and the associated LRT [101] will be used to test hypothesis *2.1* if a significant adaptive shifting is detected in the PEER group compared with the control group. The GLMM can address the group heterogeneity by specifying the corresponding covariance structure in random effect terms.

To test hypothesis *2.2*, positive shift in their perceptions of aging, the longitudinal mixed model analysis of variance will be used to test the effects of the intervention by comparing the PEER group with the control group from all follow-up assessment visits. Measurements, such as the negative self-perceptions of aging, can be incorporated into the GLMM model to investigate their potential role as mediators of FRA shifting and examine the effects of the intervention.

Aim 3 is to explore participants’ experiences with the intervention and potential barriers to access and adoption of the technology-based PEER intervention to inform future research.

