### Power Analysis and Sample Size

The sample size estimate was based on the primary outcomes of fall risk (CDC fall risk score) and PA (normalized MVPA) for aim 1 and the secondary outcome of FRA shifting (BBS score) for aim 2. The difference in the normalized mean MVPA between the PEER group (mean 3.67, SD 2.54) and the control group (mean 5.38, SD 2.68) and the difference in the fall risk score between the PEER group (mean 2.72, SD=3.23) and the control group (mean 2.21, SD=2.06) are considered markers of PA and fall risk, respectively. Considering a clinically relevant normalized difference in MVPA of 1.7 (SD 2.60) and a fall risk score difference of 0.50 (SD 2.56), the medium effect size Cohen *d*=0.25, intraclass correlation (ICC) of 0.8, and a significance level of are used for the calculation of the sample size. A sample size of 120 participants per arm is needed to reach 80% statistical power to detect the difference between the PEER and control groups on repeated measures of normalized MVPA. A sample size of 120 participants per arm is needed to reach 80% statistical power to detect the difference between the PEER and control groups on repeated measures of normalized MVPA.

In addition, the sample size was also based on the following: (1) at least 3 sites per arm; (2) an initial hypothesis that at least 10% (34/340) of the irrational, incongruent, and congruent FRA would shift to rational FRA after PEER completion; (3) an approximate study adherence rate of 80% [56], and (4) an estimated study dropout rate of approximately 40% (136/340) over time. Therefore, the sample size was increased from 120 to 170 per arm, resulting in a total of 340 participants. On the basis of our pilot study [26], we estimate that approximately 60% (204/340) of the low-income older adults will meet all inclusion and exclusion criteria and will be interested in participating in this study. We estimate that a minimum of 567 low-income older adults will be screened to identify 340 low-income older adults for enrollment, and approximately 240 low-income older adults (120 per arm) are needed to complete the study. Given the sample size of 120 per arm, a significance level of *P*=.05, and 80% power, considering a clinically relevant BBS mean score difference of 8 (SD 12), the effect size Cohen *d*=0.36 can be achieved to compare the intervention effect based on secondary outcomes.

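### The Aim 1 model treats T1 as one of four outcomes, so baseline enters at best as a change from T1; entering it as a covariate for T2-T4 is more efficient, and the tested arm term needs naming

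*Protocol article*

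**What the plan says.** All statements are in the protocol article, Data Analysis, Aim 1.

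- **Outcome vector.** Fall risk, dynamic balance and accelerometer-based activity are modelled "as longitudinal outcomes consisting of 4 measurements (baseline or T1, after program completion or T2", then T3 and T4. Baseline is thus a response in the linear mixed model.
- **Test.** For H1.1, "the likelihood ratio test (LRT) [101] associated with LMM will be used from all follow-up assessment visits". H1.2 and H1.3 are tested in the same way. No parameter, degrees of freedom or visit weighting is given.
- **Interaction.** "To determine the impact of the PEER intervention during follow-up evaluations, the group-by-time interaction term will be incorporated into the model".
- **Covariates.** Where possible, "the models should be modified to account for relevant factors such as age, sex, general health perception, and the number of falls" before baseline. The list is open and does not name the T1 value of the outcome.

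Nothing constrains the T1 means of the two arms to be equal. Recruitment, Randomization, and Procedures plans 3 sites per arm, with the allocation of sites revealed before participants are recruited.

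**The concern.** A test built on follow-up visits does not sit squarely with a model in which T1 is a fourth response. If the group-by-time term carries the treatment effect, the model compares change from T1 between arms. That removes a T1 difference but subtracts the whole T1 value, noise included. A regression on T1 subtracts only the part that predicts follow-up, so its residual variance is never larger under the usual equal-variance assumptions.

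Two things are at stake. One is precision that the trial has already paid for, since T1 is collected on everyone. The other is a defined primary test: a three-parameter interaction and a single averaged difference both fit the wording, and they behave differently when the effect fades.

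**Working it through.** **Inputs.** Power Analysis and Sample Size gives 120 per arm, d=0.25, an ICC of 0.8, a fall risk difference of 0.50 (SD 2.56) and an MVPA difference of 1.7 (SD 2.60). Hence d = 0.50/2.56 = 0.195 for fall risk and 1.7/2.60 = 0.654 for MVPA. Alpha is 0.05 from Data Analysis, taken as two-sided; the figure is absent from the sample-size sentence as read.

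Assumptions: 0.8 is the correlation ρ between visits within a person (the article does not say so), compound symmetry with equal variances, and no site variance until step 4.

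**1. The plan's own figure.** With n per arm = 2(1.960+0.842)²·V/d², d=0.25 and ρ=0.8:

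| Analysis | V | n per arm |
|---|---|---|
| single visit | 1 | 252 |
| mean of four visits | (1+3ρ)/4 = 0.85 | 214 |
| mean of T2-T4 | (1+2ρ)/3 = 0.867 | 218 |
| change to one visit | 2(1-ρ) = 0.40 | 101 |
| one visit adjusted for T1 | 1-ρ² = 0.36 | 91 |
| change to mean of T2-T4 | 0.867+1-2ρ = 0.267 | 67 |
| mean of T2-T4 adjusted for T1 | 0.867-ρ² = 0.227 | 57 |

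None gives 120, so the article's figure does not reveal which test was intended. I take 120 per arm as given.

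**2. Like-for-like gain, constant effect at T2-T4.** For both the 1-df averaged contrast and the 3-df test, the noncentrality is λ = d²·(120/2)/V, with V = 0.267 for change and 0.227 for adjustment at ρ=0.8. At ρ=0.5 the two values are 0.667 and 0.417.

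| Case | λ change → adjusted | 3-df power | 1-df power |
|---|---|---|---|
| d=0.25, ρ=0.8 | 14.06 → 16.54 | 89.8% → 94.2% | 96.3% → 98.2% |
| d=0.195, ρ=0.8 | 8.58 → 10.10 | 69% → 77% | 83% → 89% |
| d=0.25, ρ=0.5 | 5.62 → 9.00 | 49% → 71% | 66% → 85% |
| d=0.654, ρ=0.8 | 96.2 → 113.2 | above 99% in both | above 99% in both |

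**3. Fading effect (0.25, 0.125, 0 at T2, T3, T4; ρ=0.8).** The sum of squares is 0.0781 and the sum is 0.375.

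- 3-df change: λ = (0.0781 - 0.375²/4)·60/0.2 = 12.9, power 86.8%.
- 3-df adjusted: λ = (0.0781 - 0.375²·0.8/3.4)·60/0.2 = 13.5, power 88.4%.
- 1-df averaged change: λ = 0.125²·60/0.267 = 3.5, power 46.6%.
- 1-df averaged adjusted: λ = 0.125²·60/0.227 = 4.1, power 52.9%.

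Adjustment still helps within each pair, but averaging costs far more than adjustment gains.

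**4. Site variance (assumed, as the article gives none).** Let s be the share of variance left between sites, the same for both analyses. The variance of the arm difference is about 2(V/120 + s/3), tested with t on 4 df. For the 1-df contrast at d=0.25, ρ=0.8:

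| s | change | adjusted |
|---|---|---|
| 0 | 80% | 85% |
| 0.01 | 44% | 46% |
| 0.02 | 30% | 31% |
| 0.05 | 17% | 17% |

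**The case against.** The strongest defence is that the planned model is a standard longitudinal one and already uses baseline: with T1 in the response vector, the interaction compares change from T1. That stands. A reader might infer that baseline goes unadjusted and that a T1 imbalance would count as treatment effect. The text does not support this, because the impact at follow-up is assigned to the interaction.

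A reader might also compute the power of an arm effect averaged over all four visits, 35% at d=0.25 and 23% for fall risk, and conclude that the trial is badly underpowered by its choice of test. That requires a test that includes T1, while the article places the test on follow-up visits and adds the interaction. Those figures should not be used against the plan.

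Nor is a single averaged contrast plainly superior. Study Design asks whether effects are maintained without ongoing intervention, and under the fading pattern the averaged adjusted contrast has 52.9% power against 86.8% for the planned 3-df interaction.

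Finally, the exact contrast may be set in an analysis plan that is not shown, and the covariate list is open. That is fair against a complaint of missing detail. It does not answer the point that the article does fix T1 as an outcome, which is the less efficient use of it.

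One caution applies to the remedy. Because participants are recruited after site allocation is revealed, equal T1 means are not assured. A model that imposes a common T1 mean builds that assumption in, so the covariate form is preferable. Neither form repairs selective recruitment.

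**Conclusion.** The point holds as a modest, inexpensive improvement in efficiency together with a clarification of the primary test. Comparing tests of equal degrees of freedom, adjustment for T1 gains about 2 to 4 points at d=0.25 and 5 to 8 points for the fall risk effect. For fall risk the 3-df test stays below the planned 80% either way (69% against 77%). At d=0.25 the gain rises to 19 to 22 points if the correlation is 0.5 rather than 0.8, and it is negligible for the raw MVPA difference.

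These sizes rest on a constant effect, on 0.8 being a within-person correlation, and on no site variance. With 3 sites per arm, the gain on the 1-df contrast falls to about 2 points at an assumed residual site share of 0.01 and to almost nothing at 0.05. Adjustment was never worse in the cases run. The choice between an averaged and a joint test is a separate matter and depends on the expected effect pattern.

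**What to change.** For each primary outcome, model T2, T3 and T4 as responses with that outcome's T1 value as a covariate and a site random effect. Prefer this to a model with a common T1 mean. State which arm term over T2-T4 the likelihood ratio test examines: the averaged difference if a sustained effect is expected, or otherwise the joint test of the follow-up differences. State it before outcome data are seen.

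The cost is one or two sentences of analysis wording. T1 is already collected, and no visit, measurement or participant is added.
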